## Abstract

Healthcare workers (HCWs) are at increased risk of infection by the virulent severe acute respiratory syndrome coronavirus-2 (SARS-CoV-2). Though data exist on the positivity rate of the SARS-CoV-2 reverse transcription polymerase chain reaction (RT-PCR) test as well as COVID-19-related deaths amongst HCWs in South Africa, the overall infection rate remains underestimated by these indicators. It is also unclear whether the humoral immune response after SARS-CoV-2 infection offers durable protection against reinfection. This study will assess the SARS-CoV-2 seroprevalence amongst HCWs in the Eastern Cape (EC) and examine the longitudinal changes (rate of decay) in the antibody levels after infection in this cohort. Using a multi-stage cluster sampling of healthcare workers in selected health facilities in the EC, a cross-sectional study of 2250 participants will be recruited. In order to assess the community infection rate, 750 antenatal women in the same settings will be recruited. Relevant demographic and clinical characteristics will be obtained by a self-administered questionnaire. A chemiluminescent microparticle immunoassay (CMIA) will be used for the qualitative detection of IgG antibodies against SARS-CoV-2 nucleocapsid protein. A nested cohort study will be conducted by performing eight-weekly antibody assays (X2) from 201 participants who tested positive for both SARS-CoV-2 RT-PCR and serology. Logistic regression models will be fitted to identify the independent risk factors for SARS-CoV-2 infection. The cumulative SARS-CoV-2 infection rate and infection fatality rate among the frontline HCWs will be estimated. In addition, the study will highlight the overall effectiveness of infection prevention and control measures (IPC) per exposure sites/wards at the selected health facilities. Findings will inform the South African Department of Health’s policies on how to protect HCWs better as the country prepares for the second wave of the SARS-CoV pandemic.

## 1. Introduction

Healthcare workers (HCWs) are a high-risk group for severe acute respiratory syndrome Coronavirus-2 (SARS-CoV-2) infection owing to occupational exposure to large numbers of highly infectious patients with COVID-19 disease (mostly pneumonia) requiring hospitalization for supportive oxygen therapy [1]. Despite infection prevention and control (IPC) measures including isolation of cases and the use of personal protective equipment (PPE), HCWs still acquire the infection at a higher rate than the general population. A prospective study of 200 frontline HCWs in London during the peak of viral transmission showed that 44% became infected, more than double that of the local population [2]. A smartphone application survey of almost 100,000 HCWs from the United Kingdom (UK) and United States of America (USA), and over two million members of the general public, with self-reporting of positive reverse transcription-polymerase chain reaction (RT-PCR) for the SARS-CoV-2 infections was performed [3]. It found an almost twelve-fold increased risk (HR = 11.6, 95% CI: 10.9–12.3) of acquiring SARS-CoV-2 among the frontline healthcare workers (HCWs) in comparison with the general population.

In South Africa, HCWs are considered as priority group for daily symptom screening and testing for any potential COVID-19 symptoms [1]. The cumulative prevalence of SARS-CoV-2 infection among HCWs is unknown, given that PCR test is often limited to symptomatic individuals. While this is a source of concern for administrators of the South African Department of Health, it is not clear whether the hazard risk reported by Nguyen et al. [3] is translatable to HCWs in the sub-Saharan African region, where regional risk may vary. There is value in the local seroprevalence testing of HCWs to assess more adequately the extent of SARS-CoV-2 infections (symptomatic and asymptomatic), and to compare this to a group more representative of the community (ante-natal women for the purpose of this study). Such a study was performed in Denmark, where 28,792 HCWs and 4672 blood donors had SARS-CoV-2 IgM/IgG testing. Seroprevalence was higher in HCWs than in blood donors (4.04% vs. 3.04%; risk ratio (RR) 1.33 (95% CI 1.12–1.58); *p* < 0.001). Male HCWs working in the hospitals, and in dedicated COVID-19 wards, were all significant and independent risk factors for the disease [4].

Due to the high exposure environment of hospitals, accurate data on the cumulative infection rate amongst HCWs will add to the existing literature on SARS-CoV-2 transmission dynamics. Quantifying risk factors for infection amongst HCWs can be instructive for future prevention interventions. Reported inadequate PPE availability and use has been shown to significantly increase risk for infection [3,5]. Within the health facilities, high exposure clinical areas (Accident and Emergency, acute medical ward, and intensive care units) have been associated with increased infections compared to administration or support services [4]. In contrast, other studies have shown no difference between different staff roles, suggesting that most infections are acquired outside of contacts with patients, or outside of the hospital environment [6,7,8].

Having at least one co-morbidity in a HCW was shown to be a significant risk for acquiring COVID-19 in one study [7]. Outside of the health care environment, a general practitioners (GP) network study of 3802 SARS-COV-2 tests performed in the UK, showed significantly increased infections among males, age 40–64 years, black ethnicity, lower socio-economic status, chronic kidney disease patients, and the obese. Interestingly, smokers had a lower risk of infection. [9] (de Lusignan et al. 2020). It is unclear whether the risk factors for acquiring SARS-CoV-2 infection among HCWs in South Africa will follow similar socio-demographic patterns reported in the rest of the world.

Molecular testing (RT-PCR) of respiratory samples (naso/oropharyngeal swab, sputum, and bronchoalveolar lavage) is the recommended diagnostic modality for confirming acute SARS-CoV-2 infection [1]. The limitation of this test, however, is the significant proportion of false negative tests, resulting in under-estimation of true infection prevalence. Asymptomatic infection is also frequent, occurring in 46% (95% CI: 18.48–73.60%) of cases in one meta-analysis [10]. Testing strategies that focus on symptomatic individuals (as were adopted by the South African Department of Health [1]) will always under-estimate the true population burden of the disease and negatively impact on adequate planning of IPC measures for the country.

A wide array of commercial and research SARS-CoV-2 antibody tests have been developed since the identification of the virus. They measure antibodies that target specific viral epitopes (nucleoprotein, spike protein, and receptor-binding domain) and measure immunoglobulin A, M, or G. IgG is the last antibody to rise in response to acute infection, but it persists the longest [11]. Serological testing includes lateral-flow antibody assays, beadbased assays (Luminex technology), enzyme-linked immunosorbent assays (ELISAs), and automated serology platforms. The two basic categories of serological tests currently available for COVID-19 are rapid diagnostic tests (also known as point-of-care tests) and formal laboratory serological tests. Rapid diagnostic tests often use the lateral flow design, which produces a color change on a test strip. The formal assays are either based on the ELISA or the chemiluminescent detection principle. At least three of these assays, available in South Africa, are produced by by Euroimmun, Roche Diagnostics, and Abbott Diagnostics.

A Cochrane review of 54 studies of laboratory and point-of-care assays reported pooled results for IgG/IgM sensitivity of 30.1% (95% CI 21.4–40.7) for 1 to 7 days, 72.2% (95% CI 63.5–79.5) for 8 to 14 days, and 91.4% (95% CI 87.0–94.4) for 15 to 21 days after the onset of illness. Between 21 and 35 days, pooled sensitivities for IgG/IgM were 96.0% (95% CI 90.6–98.3) [11]. Antibody testing is therefore only recommended after 14 days of symptoms in acute infection and has greater utility in late infection or to assess previous SARS-CoV-2 exposure or in seroprevalence surveillance.

Areas of uncertainty with SARS-CoV-2 antibody testing, is how long the IgG antibody levels remain detectable in the blood and the durability of humoral immune response post-infection. Early reports of serial antibody testing in recovering COVID-19 cases indicated an apparently short-lived antibody response. One study of 34 mild cases reported a half-life of 36 days for IgG levels measured over approximately 90 days [12]. In contrast, a recent seroprevalence study was performed on over 30,000 Icelanders, including 1797 RT-PCR confirmed COVID-19 cases, using six different antibody assays. This study demonstrated good IgG antibody durability, with levels rising to two months post-infection, and then sustained up to four months (the study cut-off) [13]. It is therefore unclear whether there are regional or ethnic variations in the durability of SARS-CoV-2 antibodies. The proposed study aims to estimate the cumulative SARS-CoV-2 infection rate and will further examine the durability of the humoral immune response specific to this virus in a cohort of HCWs in the Eastern Cape, South Africa.

## 2. Protocol

This study protocol will be implemented in accordance with the recommendations outlined in the STROBES (Strengthening the Reporting of Observational Studies in Epidemiology) checklist. The use of the STROBES framework will guarantee a high scientific standard.

### 2.1. Design and Settings

This study will adopt a cross-sectional survey with a nested prospective cohort component. Four health facilities have been purposively selected across the Eastern Cape Province, South Africa, for this study. All the three tiers of health care facilities are represented; Frere Hospital (tertiary), Cecilia Makiwane Hospital (regional), and two primary healthcare centers: Nontyatyambo and Empilweni Gompo Community Health Centers (CHCs). Findings will provide guidance on the overall infection rates amongst HCWs across the three tiers of health facilities in the province.

### 2.2. Participants

The study population will include all categories of HCWs at the selected health facilities. Given the large number of HCWs (doctors, nurses, allied health workers, and administrative staff) in the regional (about 1400 staff) and tertiary (about 1500 staff) hospitals in comparison to those in the primary health care (about 120 staff), it is expected that the majority of the participants in this study will be recruited from the two large hospitals. Since this cross-sectional study aims to provide mass screening (using a SARS-CoV-2 serological test) for all HCWs, about 2250 HCWs are expected to take part in this study. The estimated number of participants per study site is proportional to the overall count of HCWs at each site. A total of 750 antenatal women will be recruited from the study sites to provide data on the community infection rate. The recruitment of HCWs is pre-stratified for inclusivity and is proportionate to the total head count of staff in each facility as shown in Table 1.

### 2.3. Study Procedure

All HCWs will be eligible to participate in this study. Using a multi-stage cluster sampling technique, participants’ clusters will be categorized by the facility of employment (Table 1) and exposure areas. Participants will be conveniently sampled within each cluster. Every HCW in each cluster will be given an equal opportunity to be sampled into the study, and participation will be purely voluntary.

Participants will be recruited from the study sites concurrently in order to avoid time variations in the main outcome measures. For inclusivity, exposure areas are pre-defined in accordance with risk assessment by Iversen et al. [4]:High risk: Accident and Emergency unit, acute respiratory (person under investigation/COVID-19) wards and intensive care units (ICU).Intermediate risk: non-respiratory admission wards, outpatient departments (OPDs) and other clinical areas.Low risk: administration offices and other non-clinical areas.

Information about this mass screening will be disseminated through the departmental heads and clinical managers. Each working areas/unit will be allocated specific days to give allowance for those on duty as well as those off-duty to participate with minimal interruptions in patient care. Each participant will complete a self-administered questionnaire. In addition, medical records of deceased HCWs during the pandemic will be reviewed in order to estimate the case fatality rate of HCWs in the study sites.

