## 3. Statistical Analysis

Data will be exported from Redcap to the STATA Version 15 (Stata Corp., College Station, TX, USA) and cross-checked for completeness and accuracy. Incomplete data will be re-verified, and where possible, the OHS and NHLS databases will be reviewed to maximize the chances that data for the main outcome measures are collated accurately. Multi-level analysis will be performed on all the participants; those with complete and incomplete results. Differences in the baseline (demographic and clinical) characteristics of the two groups will be compared by using Pearson chi-square and Fisher’s exact test for bivariate analysis.

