## Figures and Tables

**Table 1 ijerph-18-00323-t001:** Proposed recruitment of healthcare workers (HCWs) into the study.

Sites	HCWs (*n*)	Antenatal Women (*n*)
Frere Hospital	1100	400
Cecilia Makiwane Hospital	1000	350
Nontyatyambo CHC	75	-
Empilweni Gompo CHC	75	-

CHC: Community health centre.

**Table 2 ijerph-18-00323-t002:** Proposed study schedule.

Tasks	Sept., 2020	Oct., 2020	Nov., 2020	Dec., 2020	Jan., 2021	Feb., 2021	Mar., 2021	Apr., 2021
Design of protocol and ethical approvals								
Protocol implementation (baseline recruitment)								
Data analysis								
Follow-up study implementation								
Data analysis of follow-up study								
Stakeholder engagement								
Completion of project								

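### Staff enter the survey by convenience and voluntarily, and the plan never compares participants with the roughly 25–28% expected to stay out, so selection bias in the infection rate goes unassessed

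*Protocol article*

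**What the plan says.** Section 2.2 takes all categories of staff at the four facilities as the study population. It expects a large but partial take-up: "about 2250 HCWs are expected to take part in this study". The head counts are given "in the regional (about 1400 staff) and tertiary (about 1500 staff) hospitals" and "in comparison to those in the primary health care (about 120 staff". Table 1 sets targets of 1100 and 1000 for the two hospitals and 75 for each of the two health centres.

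Section 2.3 labels the design multi-stage cluster sampling, with clusters formed by facility and exposure area. It then says "Participants will be conveniently sampled within each cluster", followed by "Every HCW in each cluster will be given an equal opportunity to be sampled into the study, and participation will be purely voluntary". Each unit is allotted several days so that staff on and off duty can attend.

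Section 3 defines who is analysed: "Multi-level analysis will be performed on all the participants; those with complete and incomplete results". The baseline comparison that follows is between those two groups of participants. The missing-at-random assumption in Section 3.1 concerns missing data in the regression models.

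The estimate is put to wide use. Section 3.1 takes it as the overall infection rate and builds a fatality rate per facility on it. Section 2.1 offers it as guidance on infection rates across three tiers of care in the province. Section 7 suggests that rates by exposure area might guide staff allocation.

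**The concern.** Giving everyone the same invitation does not equalise the chance of inclusion when each person decides whether to come. The decision may be linked to the outcome, because Section 2.9 promises every participant a personal result. Someone who had an untested illness may want to know. Someone already confirmed by PCR may see no need. Someone isolating or on sick leave may be absent on the allotted days. These forces pull in different directions, so the net bias could have either sign.

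Nothing in the article would reveal it. Targets proportional to facility size balance the facilities, but not infection history within a facility. Comparing complete with incomplete participants says nothing about staff who never took part.

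At stake is the primary estimate. The fatality rate sets deaths taken from the sites' records against an infection rate taken from volunteers, so any selection error passes into it. If participation differs by exposure area, the overall rate is also affected by the mix of areas among those who came.

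**Working it through.** **Inputs.** Targets are from Table 1 and head counts from Section 2.2. The 45% is the planning figure for the nested cohort in Section 2.10, used here only as an illustration. The 4.04% is the Danish healthcare-worker seroprevalence cited in Section 1. Differences between participants and non-participants are my assumptions, since the article gives none.

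**1. The plan's own figure.** 1100 + 1000 + 75 + 75 = 2250, which reproduces.

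**2. Share not taking part.**
- If 120 is the primary-care total: 1500 + 1400 + 120 = 3020 staff; 3020 − 2250 = 770; 770/3020 = 25.5%.
- If 120 is per centre: 1500 + 1400 + 240 = 3140 staff; 3140 − 2250 = 890; 890/3140 = 28.3%.
- Table 1 plans 75 + 75 = 150 from the two centres. That is 125% of 120 but 62.5% of 240, so the text and the table must be reconciled.

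**3. Bias.** Let f be the participation fraction and d the prevalence in participants minus that in non-participants. The staff-wide rate is p − (1 − f)d, so the bias of the participants' rate p is (1 − f)d = 0.255d. A 10-point difference gives 2.5 points (2.55 before rounding down) and a 20-point difference gives 5.1.

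**4. Sampling half-width at 45%.** 1.96 × √(0.45 × 0.55/2250) = 2.06 points, a full width of 4.1 points.

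**5. Where bias matches sampling error.**
- Half-width: 2.06/0.255 = 8.1 points (2.06/0.283 = 7.3 with 3140 staff).
- Full width: 4.11/0.255 = 16.1 points (4.11/0.283 = 14.5 with 3140 staff).

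**6. Dependence on prevalence.** Assume that non-participants have 0.5 to 1.5 times the participants' prevalence, with 3020 staff. The maximum bias is then ±0.255 × 0.5 × p.

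| Prevalence in participants | Maximum bias (points) | Sampling half-width (points) |
|---|---|---|
| 45% | ±5.7 | ±2.1 |
| 20% | ±2.5 | ±1.7 |
| 10% | ±1.3 | ±1.2 |
| 4.04% | ±0.5 | ±0.8 |

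These are ordinary binomial half-widths. If the interval treated the staff as a finite population, each would shrink by √(1 − 2250/3020) = 0.505, to about ±1.04 points at 45% and ±0.41 at 4.04%. The ordinary interval is therefore the more lenient benchmark for selection.

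**7. Limits with no information on non-participants, at 45%.** Lower: 0.45 × 0.745 = 33.5%. Upper: 33.5% + 25.5% = 59.0%. With 3140 staff the limits are 32.2% and 60.6%.

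**8. Effect on the fatality rate.** Suppose deaths are divided by infection rate × head count, and the rate of 45% is 2.06 points too high. The fatality rate is then 42.94/45 = 0.954 of its proper value, about 5% too low.

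**The case against.** The voluntary nature is disclosed: the sentence on equal opportunity itself ends by saying so, and the one before it admits convenience selection. Equal opportunity can fairly be read as equal invitation. A reader might infer that the plan promises equal selection probabilities, but the text does not go that far. What stands is narrower: equal invitation does not remove self-selection, and the cluster-sampling label suggests more than the procedure delivers.

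The article also takes steps to widen access. Several days per unit, for staff on and off duty, should reduce missed attendance. Section 5 bars use of serology results for compensation claims, which removes one motive for selective volunteering. Both help, but neither addresses a wish to know, or not to know, one's own status.

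An article condenses a fuller plan, and weighting for non-participation could be set out there. This point does not rest on that silence alone. The article itself fixes convenience selection, restricts the analysis to participants, names its group comparison, and still uses the result as the overall infection rate.

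The size is assumption-driven, and that objection is sound. The 45% comes from London and sized a different component. The differences in step 6 have no source in the article, and the quarter is a planned shortfall rather than observed refusal.

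**Conclusion.** The concern holds in a limited form. Followed as written, the plan cannot detect selection among the 25–28% of staff expected to stay out, and the resulting rate feeds the facility fatality rates. At an illustrative 45% prevalence, a difference of about 8 points between participants and non-participants gives a bias equal to the sampling half-width of ±2.1 points. It takes about 16 points to equal the full width of the interval.

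Three stronger readings are not supported:

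- **Selection dominates the error.** This depends on prevalence and on assumed differences. At about 4%, with a 50% relative difference, bias is about 0.5 points against ±0.8 from sampling.
- **The bias has a known sign.** The plausible mechanisms oppose one another, and the article gives no data.
- **The occupational health and laboratory (OHS and NHLS) records already hold a complete count of PCR-positive staff.** Sections 2.8 and 3 use them to fill gaps in study data. The epidemic curve in Section 3.1 may include non-participants, but no comparison is planned from it.

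The survey remains useful. The design description and the treatment of non-participation should be corrected before its rate is presented as that of the facilities.

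**What to change.** - Describe the design in Section 2.3 as a voluntary survey of all staff at four purposively chosen facilities, and say equal invitation where that is meant.
- Reconcile the 120 primary-care staff in Section 2.2 with the 150 planned in Table 1, so that the denominator is clear.
- Report participation by facility and exposure area against staff head counts. The article gives facility-level counts only, so aggregate counts by exposure area would have to be requested.
- Post-stratify the seroprevalence estimate to those head counts, carry it into the fatality rate, and show both beside the unweighted figures.
- Add a sensitivity range over stated prevalence ratios for non-participants, for example 0.5 to 1.5. Post-stratification corrects only for differences between cells. It cannot remove selection on infection history within a cell, so the range is needed as well.
- If the OHS and NHLS records prove to give a usable staff-wide PCR-positive count per facility, compare participants with it or calibrate to it.

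The cost is obtaining aggregate counts, one added weighting step, and a somewhat wider interval. No additional participants or blood samples are needed.

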### 2.4. Study Instrument

The questionnaire for this study was purposively designed to capture data that are relevant to the study objectives, using validated measures from the World Health Organization (WHO) STEPwise tool [14], COVID-19 risk assessment tool [15,16], persistence of symptoms [17] and vaccine hesitancy survey tool [18]. The questionnaire comprises variables on demographics, exposure risks, vulnerability risks, prior SARS-CoV-2 PCR tests and results, COVID-19 symptoms and management, post-COVID-19 persistent symptoms, and perception about the COVID-19 vaccine.

